## Abstract

**Background:**

Low-back pain is one of the most common health conditions worldwide. It is defined as pain below the costal margin and above the inferior gluteal folds. Current guidelines recommend management of chronic health (e.g., low back pain) conditions in older people at primary health care settings using active strategies (e.g., exercise). In non-specific low back pain, high quality evidence supports active strategies for general population. However, the management of non-specific low back pain in the older people has been overlooked and evidence is limited to a small number of low powered randomized controlled trials with high risk of bias.

**Methods:**

This is a prospectively registered, open, two-arm randomised controlled trial comparing the group-based exercise and waiting list in pain intensity (11-item Pain Numerical Rating Scale) and disability (Roland Morris questionnaire) of older people (i.e., 60 years old or over) with chronic non-specific low back pain. One hundred and twenty patients will be recruited from Diamantina, Brazil. Follow-ups will be conducted in post-treatment (8 week) and 6- and 12-months post-randomisation.

**Discussion:**

Our hypothesis is that group-based exercise will be better than waiting list in reducing pain intensity and disability in older people with chronic non-specific low back pain.

**Impact:**

The practice of individualized exercise has been studied for the management of chronic non-specific low back pain in older people. However, the group exercise, even showing high quality evidence for the improvement of several important outcomes in this population, has been ignored until now. Thus, the results of this study have the potential to indicate a viable and accessible strategy for managing chronic non-specific low back pain in the older people.

**Trial registration:**

The study was prospectively registered at www.ensaiosclinicos.gov.br (RBR-9j5pqs). Date-11/18/2020.

## 1. Background

Low-back pain (LBP) is one of the most common health conditions worldwide [1]. It is defined as pain below the costal margin and above the inferior gluteal folds, with or without referred leg pain [2, 3]. It is expected that 70% to 85% of the general population will present an episode of LBP during lifetime, including older people (i.e., 60 years old or over) [4, 5]. The most common form of LBP is non-specific [6], defined as the symptoms without a specific cause [7, 8]. Older people with chronic non-specific (CNS) LBP reports disability [9, 10], productivity loss [11] and low quality of life (QOL) [12].

Current guidelines recommend management of chronic health conditions in older people at primary health care settings using active strategies (e.g., exercise) to decrease pain intensity, disability, productivity loss and health care costs [3, 13, 14]. In primary health care, group-based exercise is often used to manage older people [15, 16] because it has shown to be cost-effective for older people with different health conditions [17–19]. For instance, this active strategy is effective for prevention and fear of falling [17, 18], improvement of QOL [17] and balance [17, 20] in the older population.

In CNSLBP, high quality evidence supports active strategies such as exercise for general population [3, 14, 21–25]. Previous systematic reviews also showed promising efficacy of exercise on pain intensity and disability related to CNSLBP in older people [26]. However, the management of CNSLBP in this population has been overlooked and evidence is limited to a small number of low powered randomized controlled trials with high risk of bias [27, 28]. Moreover, efficacy of group-based exercise has not been investigated in older people with CNSLBP [26, 28]. Thus, the primary aim of this randomized controlled trials is to investigate the efficacy of an 8-week group-based exercise program on pain intensity and disability in older people with CNSLBP in a primary health care setting. Our secondary aims are to investigate efficacy on global impression of recovery, frequency of falls, fear of falling and physical activity (PA) level.

## 2. Methods

### 2.1 Elaboration protocol

This protocol was developed in accordance with the SPIRIT guidelines [29] and is reported according to the CONSORT statement [30]. The schedule with assessment at different points in time is shown in Fig 1.

**Fig 1 pone.0266613.g001:**
[figure not shown]
SPIRIT schedule of assessments at different time points.

### 2.2 Study design

**The Exercise for chronic back pain in older people (ESCAPE) trial** is a prospectively registered, open, two arm randomised controlled trial.

### 2.3 Settings and eligibility criteria

The study will be conducted at primary health care centers in Diamantina, Brazil. Participating in the study are patients aged 60 years old or over who seeks primary health care or a university outpatient physical therapy center in Diamantina, Brazil. The inclusion and exclusion criteria are as follows:

The inclusion criteria:

Older people aged 60 years old or over who have CNSLBP, defined as pain below the costal margin and above the inferior gluteal folds, for at least 3 months [2, 3]; andDisability scores 4 out of 24 points or higher in the Roland-Morris Disability Questionnaire (RMDQ) and pain intensity scores 3 out of 10 points or higher in a 11-point numeric rating scale [31].

The exclusion criteria:

Suspected or confirmed serious spinal pathology (fracture, metastatic, inflammatory or infective diseases of the spine, cauda equina syndrome/widespread neurological disorder);Radiculopathy (i.e., degree 2 of strength, reflex or sensation affected for same nerve root);Previous history of spinal surgery in the last 12 months; scheduled for major surgery during the study or at the follow up period;Indicative of cognitive deficit validated by the Mini Mental State Examination; andContraindications to exercise listed of the American College of Sports Medicine (ACSM) guidelines (Table 1) [32].

**Table 1 pone.0266613.t001:** Contraindications to exercise testing.

**ABSOLUTE**
➢ A recent significant change in the resting electrocardiogram (ECG) suggesting significant ischemia, recent myocardial infarction (within 2 d), or other acute cardiac event ➢ Unstable angina ➢ Uncontrolled cardiac dysrhythmias causing symptoms or hemodynamic ➢ compromise ➢ Symptomatic severe aortic stenosis ➢ Uncontrolled symptomatic heart failure ➢ Acute pulmonary embolus or pulmonary infarction ➢ Acute myocarditis or pericarditis ➢ Suspected or known dissecting aneurysm ➢ Acute systemic infection, accompanied by fever, body aches, or swollen lymph glands

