**RELATIVE (must consult a doctor before participation)**
➢ Left main coronary stenosis ➢ Moderate stenotic valvular heart disease ➢ Electrolyte abnormalities (*e*.*g*., hypokalemia or hypomagnesemia) ➢ Severe arterial hypertension (*i*.*e*., systolic blood pressure [SBP] of _200 mm Hg and/or a diastolic BP [DBP] of _110 mm Hg) at rest ➢ Tachydysrhythmia or bradydysrhythmia ➢ Hypertrophic cardiomyopathy and other forms of outflow tract obstruction ➢ Neuromotor, musculoskeletal, or rheumatoid disorders that are exacerbated by exercise ➢ High-degree atrioventricular block ➢ Ventricular aneurysm ➢ Uncontrolled metabolic disease (*e*.*g*., diabetes, thyrotoxicosis, or ➢ myxedema) ➢ Chronic infectious disease (*e*.*g*., HIV) ➢ Mental or physical impairment leading to inability to exercise adequately

Note: ECG = electrocardiogram; HIV = Human Immunodeficiency Virus; BP = blood pressure

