### 2.7 Intervention

#### Group-based exercise

The group-based exercise (GBE) programme will be delivered by two physical therapists (experience in musculoskeletal rehabilitation in primary health care). The GBE comprises three sessions per week of group-based exercise in a local community center, for 8 weeks [44]. Each group session will consist of 10 to 18 participants and each exercise session will last 60 minutes and consist of four stages: (1) five minutes warm up (i.e., self-regulated walk); (2) twenty minutes of moderate intensity walking; (3) thirty minutes of resistance training for the major muscles of the leg, trunk and arm and balance exercises that progress in difficulty; and (4) five-minute cool down period (i.e., self-regulated walk). The exercise intensity will be assessed by one of the following criteria: (1) point of volitional fatigue [45] for the resistance training component; and (2) perceived effort ranging from 3 to 4 on the modified 10-point Borg scale score for the walking component [45]. The intensity will be increased along the 8-week programme following the recommendations of the ACSM guideline [32] (i.e., resistance exercise- a gradual progression of more repetitions per set; and aerobic exercise- a gradual progression of exercise volume by adjusting exercise intensity) [32].

The GBE programme was set up based on tasks that makes part of performance-based assessment instruments widely used for the evaluation of physical performance of the older people (i.e., Berg Balance Scale [46], Dynamic Gait Index [47] and Timed Up and Go [48]). In addition, exercises commonly used in primary health care groups were added [49–51]. The protocol will take place in a gymnasium and will be supervised by a trained physical therapist [52–54]. Examples of the choices of exercises are provided in the S1 Appendix.

Modifications were performed after registration of the clinical trial. We included 5 minutes of warm-up and 5 minutes of cool-down during the intervention. To reduce the risk of injury during the protocol. Furthermore, based on recommendations of the ACSM guideline, criteria were established to intensity increase along the 8-week. All these changes were made before starting to recruit participants. Furthermore, the registry has been updated and is available with new information.

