### 2.9 Implementation and study group

The project will involve primary care centers that care for older peoples with CNSLBP or a university outpatient physical therapy center in Diamantina, Brazil. Older people referred to treat the condition of interest in the included settings will be invited. If there is an interest in participating, they will undergo an eligibility screening with a physiotherapist. We hypothesise that the GBE program will benefit older peoples with CNSLBP by reducing disability, pain intensity, global impression of recovery, frequency of falls, fear of falling and PA level compared with waiting list.

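### Minor safety wording: Table 1 names myocardial infarction only within 2 days, so a stable later infarction that meets no other item is not sent to a doctor before the training programme

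*Protocol article*

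**What the plan says.** The last exclusion criterion in section 2.3 refers to contraindications to exercise and points to Table 1. The table's caption refers to exercise testing.

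- **Absolute list.** Infarction appears once, in the first bullet: "recent myocardial infarction (within 2 d), or other acute cardiac event". That bullet also covers a recent significant ECG change suggesting ischemia. Further absolute items include unstable angina, uncontrolled symptomatic dysrhythmia and uncontrolled symptomatic heart failure.
- **Relative list.** Its heading begins "RELATIVE (must consult a doctor before participation". It has 12 bullets, among them "Moderate stenotic valvular heart disease", left main coronary stenosis, high-degree atrioventricular block and ventricular aneurysm. Infarction is not among them.
- **Who applies the list.** Under section 2.9, interested people are screened: "they will undergo an eligibility screening with a physiotherapist".
- **What they are screened for.** Section 2.7 states: "The GBE comprises three sessions per week of group-based exercise in a local community center, for 8 weeks". Each session has 20 minutes of moderate walking and a half-hour block described as "thirty minutes of resistance training for the major muscles of the leg, trunk and arm", together with balance exercises. Resistance intensity is judged by the "point of volitional fatigue [45] for the resistance training component".

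**The concern.** A 2-day limit on infarction is attached to a table captioned for testing, but the table serves as the entry screen for two months of repeated training. From day 3 a clinically stable person is on neither list by name. Someone with moderate valve stenosis, by contrast, must see a doctor first. Whether the person after an infarction is excluded, referred or enrolled directly then depends on how the screening physiotherapist reads the more open-ended items.

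What is at stake is the safety of a small number of older participants, half of whom are allocated to supervised exercise that includes resistance work to fatigue. Nothing statistical is at stake: the treatment comparison, the model and the sample size are untouched.

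**Working it through.** The plan gives no figure on this point, so there is none to reproduce. The check is a reading of the text, followed by a rough estimate of how many people could be affected.

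**Reading the lists for one case.** Take a person aged 60 or over who is eligible on back-pain criteria, had an infarction on day 3 or earlier before screening, and is now stable.

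1. Absolute list, infarction item: not met, because more than 2 days have passed.
2. Absolute list, other cardiac items: unstable angina and uncontrolled dysrhythmia or heart failure are not met by a stable person. The ECG clause could apply, but the baseline assessment in section 2.4 lists no ECG. The clause on another acute cardiac event has no clear day limit. A screener might count a recent infarction under it, or might reason that infarction already has its own limit.
3. Relative list: infarction is not named. The person is referred only if there is also a listed condition, such as left main stenosis, dysrhythmia or ventricular aneurysm.
4. Remaining criteria in section 2.3: none names a cardiac event.

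So a stable person who meets no other item is not sent to a doctor under the list as printed.

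**Training dose (section 2.7).**

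- Sessions: 3 per week × 8 weeks = 24.
- Resistance and balance: 24 × 30 min = 720 min.
- Moderate walking: 24 × 20 min = 480 min.

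**How many people.**

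From the protocol: 120 participants, 60 per arm (section 2.8).

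Assumed, with no basis in the document:

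- an infarction rate of 0.5%, 1% or 2% per year;
- a window from day 3 to week 12, which is 84 − 2 = 82 days, or 82/365 = 0.225 year;
- people with a recent infarction join as readily as anyone else.

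Expected number = participants × 0.225 × rate. Chance of at least one in the exercise arm = 1 − exp(−expected number).

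| Assumed rate per year | Expected among 120 | Expected among 60 (exercise arm) | Chance of at least one in exercise arm |
|---|---|---|---|
| 0.5% | 0.13 | 0.07 | 6.5% |
| 1% | 0.27 | 0.13 | 12.6% |
| 2% | 0.54 | 0.27 | 23.6% |

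For a given rate and window these are upper bounds. They count everyone with an infarction in the window, including people a doctor has already cleared and people caught by another Table 1 item. Equal willingness to join a back-pain exercise trial soon after an infarction is also generous.

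**The case against.** The case for leaving the text alone is substantial. The authors attribute the list to a published guideline, and nothing here shows that they copied it wrongly. Several other items, and the clause on another acute cardiac event, will catch many people with a recent infarction. Training is supervised, progresses gradually, includes warm-up and cool-down, and keeps walking at a perceived effort of 3 to 4 on a 10-point scale. A fuller screening procedure may sit in a document that the article condenses.

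Most of this stands, and it keeps the point small. It does not remove it. The article prints a specific limit and a specific referral list, so the comment is about what is fixed there and not about missing detail. Attribution to a guideline does not settle whether a 2-day limit suits a training programme. The other items do not reach a stable person who has none of them.

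Three stronger readings are tempting and not supported:

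- **That the protocol contradicts itself on look-back periods.** It does exclude "Previous history of spinal surgery in the last 12 months", but that criterion sits among the spinal ones and sets no precedent for a cardiac look-back.
- **That 7% to 24% is a risk of harm, or of enrolling someone uncleared.** It is the chance that the exercise arm contains anyone with an infarction in the assumed window, before removing those already cleared or otherwise caught.
- **That the trial is unsafe, or that the guideline was misapplied.** The documents show neither, and the guideline itself is not available here.

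**Conclusion.** The point holds as a minor safety improvement in wording. Table 1 as printed lets a stable person with an infarction more than 2 days ago, and no other listed condition, enter the programme without a doctor's consultation.

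The number affected is probably close to zero: at most 0.07 to 0.27 people expected in the exercise arm under the assumed rates and window. Different rates or a longer window would move these figures, and the document does not help to choose among them. The conclusion about the text does not depend on them. No estimand, analysis or power figure changes.

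**What to change.** Leave the absolute list as it is and add one bullet to the relative list in Table 1: *Myocardial infarction more than 2 d ago, unless a doctor has already cleared the person for exercise.*

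The new bullet should not mention other acute cardiac events. These stay in the absolute list, and naming them in both places would leave it unclear which rule applies.

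Add one sentence to section 2.3 saying that relative items require a doctor's consultation and do not exclude automatically. At present the criterion cites Table 1 as a whole among the exclusions, so a screener could treat every item as an exclusion. Changing the caption from exercise testing to exercise would be a clerical tidy-up only.

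The cost is one bullet, one sentence and one line on the screening form, a few consultations through the route the protocol already has, and possibly an occasional exclusion. Because the bullet sets no upper time limit, people with a remote infarction will need to show that they have been cleared. Sample size and analysis stay as they are.

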**RELATIVE (must consult a doctor before participation)**
➢ Left main coronary stenosis ➢ Moderate stenotic valvular heart disease ➢ Electrolyte abnormalities (*e*.*g*., hypokalemia or hypomagnesemia) ➢ Severe arterial hypertension (*i*.*e*., systolic blood pressure [SBP] of _200 mm Hg and/or a diastolic BP [DBP] of _110 mm Hg) at rest ➢ Tachydysrhythmia or bradydysrhythmia ➢ Hypertrophic cardiomyopathy and other forms of outflow tract obstruction ➢ Neuromotor, musculoskeletal, or rheumatoid disorders that are exacerbated by exercise ➢ High-degree atrioventricular block ➢ Ventricular aneurysm ➢ Uncontrolled metabolic disease (*e*.*g*., diabetes, thyrotoxicosis, or ➢ myxedema) ➢ Chronic infectious disease (*e*.*g*., HIV) ➢ Mental or physical impairment leading to inability to exercise adequately

Note: ECG = electrocardiogram; HIV = Human Immunodeficiency Virus; BP = blood pressure

### 2.4 Procedure and outcome measures

All eligible older people will receive information about the study and sign an informed consent form prior to participation. Baseline assessment (in person) will include age, sex, history of falls, duration of symptoms, prognosis rating (STarT Back Screening Tool) [33], functional capacity (Short Physical Performance Battery) [34], cognitive function (Mini Mental State Examination), and the primary and secondary outcomes. Primary and secondary outcomes will be assessed (in person) again at the end of the intervention (i.e., 8 weeks after randomization) and at the 6 and 12-months follow-up. Fig 2 represents the flow of participants during the study.

**Fig 2 pone.0266613.g002:**
[figure not shown]
Flow diagram.

#### Primary outcomes

Pain intensity over the previous week (measured with a 0–10 points in numeric rating scale [NRS]): The NRS is a self-reported scale in which the patient can select one number that best describes the pain intensity. The score ranges from 0 to 10; higher scores represent higher levels pain intensity. This scale was previously validated for population with low back pain [35, 36].Disability (measured with the 0–24 points in Roland-Morris Disability Questionnaire [RMDQ]): The RMDQ is a self-reported scale of 24 items in which the patient reports pain-related disability. The score per item ranges from 1 (yes) to 0 (no). Total score ranges from 0 to 24, higher scores represent higher levels of pain-related disability. This instrument was previously validated for the low back pain Brazilian population [37, 38].

#### Secondary outcomes

Global impression of recovery (measured with the—3 to 3 Global Perceived Effect Scale [GPE]) [39]: GPE is a scale that assesses whether the patient condition has gotten worse, better, or stayed the same and to quantify the magnitude of that change. Total score ranges from—3 to 3 (i.e., -3 extremely worse, 0 unchanged and 3 fully recovered). This scale was previously validated for population with low back pain [40].Frequency of falls (number of falls during study time): All trial participants will be invited to self-complete a falls diary during study time. Falls diaries will be produced in a calendar format, printed in color on firm card. This cololette method was previously validated for the older people population [41].Fear of falling (measured with the 16–64 Falls Efficacy Scale–International [FES-I]) [42]: The FES-I presents questions about the concern with the possibility of falling when performing 16 activities, with respective scores from 1 to 4. The total score can range from 16 (i.e., no concern) to 64 (i.e., extreme concern). This instrument was previously validated for the older people Brazilian population [42].PA level (measured with the 1–7 Physical Activity Rating): Physical Activity Rating is a progressive scale with scores from 0 to 7, in which the most appropriate option for the history of physical activity in the last 30 days should be selected. Higher scores represent higher Physical Activity level. This instrument was previously validated for the older people Brazilian population [43].

### 2.5 Randomisation

The randomisation sequence to our two groups of interest (i.e., group-based exercise or control) will be computer-generated by one of the investigators who will not be involved in the recruitment of participants. The sequence will be blocked (block sizes of 4, 6, and 8, in random order). Allocation will be concealed in sequentially numbered, sealed, opaque envelopes. Participants will be stratified by gender (female or male).

### 2.6 Blinding

The statistician will be blinded to treatment allocation. The data will be coded in an unidentifiable manner and will not contain any information that can reveal what group a single participant or a group were randomised to. As this is an exercise program, it will not be possible to blind the therapist and the patient. Also, because our outcomes are Patient‐Reported Outcome Measures (PROMs), it will not be possible to blind the assessor. However, PROMs are validated and widely accepted in research and the clinic.

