### 2.11 Plan for data integrity and management

The research data will be collected by a research assistant who will be trained to collect and manage it. Participant identifiers (including name, address and contact information) will be removed from the research data and will be stored separately. Data will be entered in Microsoft Excel. Research data will be monitored weekly by scrutinising entered data. Any errors in entry will be identified (if any) and amended. Consent forms will be scanned and stored in password-protected computers of the lead researcher and at the University’s along with other research data files.

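### Section 2.6 rules out assessor blinding because outcomes are patient-reported, but that reason covers only the patient as rater, not the research assistant who collects the data in person

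*Protocol article*

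**What the plan says.** Section 2.6 of the protocol article takes the parties in turn.

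- **Statistician:** "The statistician will be blinded to treatment allocation", working on coded data.
- **Therapist and patient:** because the treatment is exercise, "it will not be possible to blind the therapist and the patient".
- **Assessor:** added as a further point. The outcomes are patient-reported, so "it will not be possible to blind the assessor".

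Section 3.2 repeats the last point as a limitation and explains it by treating the patient as the evaluator.

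Two other sections describe how the data are obtained. Section 2.4 says "Primary and secondary outcomes will be assessed (in person) again at the end of the intervention", and again at 6 and 12 months. Section 2.11 says: "The research data will be collected by a research assistant who will be trained to collect and manage it". Neither section says whether this assistant will know the allocation.

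On the measures themselves, the article says of pain: "The NRS is a self-reported scale in which the patient can select one number that best describes the pain intensity". Of disability it says: "The RMDQ is a self-reported scale of 24 items in which the patient reports pain-related disability". For falls: "All trial participants will be invited to self-complete a falls diary during study time".

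**The concern.** With a patient-reported outcome, two people can carry knowledge of the arm into the recorded value: the person who gives the rating, and the person who hands over the instrument, answers questions about it and records the result. Patient report settles the position of the first. It says nothing about the second. Section 2.6 uses a reason that applies to the rater to close the question for the assessor in general.

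In this design few other protections are left. Participants and therapists know the allocation, the comparator is a waiting list, and both primary outcomes are subjective. A data collector who knows the arm may, without intending it, explain an item differently or accept an unclear answer more readily in one group. A blinded statistician cannot remove an influence that is already in the recorded scores.

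Section 2.8 also dichotomises patients at the clinically important difference (more than 2 points on the NRS, more than 5 on the RMDQ) and derives a number needed to treat. Both scales are scored in whole points, so a change recorded as 3 instead of 2 on the NRS, or 6 instead of 5 on the RMDQ, moves a patient across the line.

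**Working it through.** The point involves no stated figure, so there is none to reproduce. The check sets the sections side by side.

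**1. Is there a person in the measurement process other than the patient?** Yes. Section 2.11 gives data collection to a research assistant, and section 2.4 makes the follow-ups face to face. The follow-ups are at 8 weeks, 6 months and 12 months, so with 120 participants there are at most 120 × 3 = 360 such visits before any dropout.

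**2. Is that person one of those whom section 2.6 rightly calls unblindable?** Not on the article's description. Section 2.7 gives delivery of the programme to two physical therapists. The research assistant is a different role.

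**3. What can the assessor in section 2.6 mean?** There are two readings.

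| Reading | Consequence |
|---|---|
| The assessor is the patient, as section 3.2 suggests | The statement is true but repeats what the section has just said about the patient. The research assistant is then covered by no blinding statement. |
| The assessor is the research assistant | The reason given does not support the conclusion. A self-rated scale does not require the person who collects it to know the arm. |

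Under either reading the data collector is left unmasked without a reason that applies to that person.

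**4. How much of the measurement could the assistant influence?** Less than in a trial with observer-rated outcomes. The article lists two primary and four secondary outcomes, 2 + 4 = 6, and none is scored by staff judgement. The NRS and RMDQ are described as self-reported and the falls diary as self-completed. What remains is influence while the scales are completed in person, and in recording the answers.

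**5. Is separation of roles compatible with the rest of the plan?** Section 2.5 already uses it: the investigator who generates the sequence takes no part in recruitment, and allocation is concealed in envelopes. Extending the principle to an assistant who is already planned needs no new post. Section 2.7 does not say who makes the weekly contact with controls, so that task would have to be given to someone else.

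**6. Can the bias be sized?** No. The documents give no input for the effect of an unblinded data collector on the NRS or RMDQ.

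**The case against.** The strongest reply is that section 3.2 makes clear whom the authors mean. If the patient is the evaluator, the evaluator is unblinded, and the article says so openly as a limitation. That stands: the limitation is true for the rater and would stay true after any change. It does not help with the research assistant, whom it leaves out.

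A second reply is that a journal article leaves staff duties to the full protocol or to operating procedures. That also stands, and the absence of a duty list is not the point here. The point is what the article does state: that blinding is not possible, for a reason that does not reach the person who collects the data.

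A third reply is that self-reported scales leave a collector little room, and that unblinded patients comparing themselves with a waiting list are the larger threat. This limits the gain but does not remove it.

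Several stronger readings are tempting and are not supported by the documents:

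- **That blinding the assistant would cost nothing.** Staffing is not described, duties would have to be arranged, and participants can disclose their group in a face-to-face visit.
- **That the assistant interviews patients, queries diaries, and enters and corrects all data.** Section 2.11 assigns collection to the assistant, but names nobody for entry, weekly checking or correction, and limits correction to entry errors.
- **That the same person will telephone the controls or attend sessions.** The article does not say so; it only fails to exclude it.
- **That every outcome will be biased toward exercise.** This is possible but not shown.

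**Conclusion.** The point holds in a limited form. Section 2.6 draws an inference that is valid for the patient as rater and invalid for the research assistant as data collector, and so gives up an avoidable source of bias in an open trial with subjective primary outcomes. The correction is worth making.

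The benefit is confined to interviewer and recording bias, and its size cannot be quantified from the documents. Expectation bias in unblinded patients compared with a waiting list remains whatever the assistant knows, so the trial would still have to be read as one with unblinded outcome ratings.

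The conclusion assumes that the assistant in section 2.11 is the person present at the in-person assessments in section 2.4, which is the natural reading, and that the assistant's duties can be kept apart from treatment delivery and control contact.

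**What to change.** In section 2.6, distinguish the patient as rater, who cannot be blinded, from the research assistant as data collector. State that the assistant who collects outcome data:

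- is not told the allocation;
- does not attend the exercise sessions;
- does not make the weekly contacts with controls.

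Have participants complete the scales themselves where they can, ask them before each visit not to disclose their group, and record each occasion on which the assistant learns it. In section 3.2, keep the limitation but confine it to the patient. If blinding the assistant turns out to be unworkable at these sites, replace the present reason with the actual one.

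**Cost:** an assignment of duties among existing staff and a short revision of two sections. Some participants will reveal their group despite being asked not to, which is why the unblinding record is needed. The change affects neither the sample size nor the analysis model.
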